**Objective 2.4**: To determine the feasibility and acceptability of utilising an accelerometer as the primary outcome in a definitive randomised controlled trial (S)	• % of accelerometers returned to research staff with valid data • Semi-structured interviews	• ≤ 70% of accelerometer data collected at 6-month post-baseline • Accelerometer data will be considered valid if it has been recorded for ≥ 10 h [42, 43] for ≥ 4/7 days, with at least one falling on a weekend [44–46] • Participants state that they believe that accelerometer is feasible and acceptable to use as the primary outcome measure in future definitive trial
**Objective 2.5**: To determine the acceptability of the patient-reported and performance-based outcome measures to participants ((S)	• Semi-structured interviews	• Participants report that they found the patient-reported and performance-based outcomes feasible and acceptable, and the time taken to complete was satisfactory for use in a definitive randomised controlled trial

Legend: *ISPACOT* Interpersonal support in physical activity consultations observational, *P* Primary feasibility outcome related to progression to definitive trial, *S* Secondary feasibility outcome

Once it has been established if each criterion has been met, further consultation with patient and public involvement (PPI) at Trial Steering Group meetings will be utilised to determine if and what modifications the intervention requires to progress to the full-scale RCT (e.g. adaptions to intervention to enable delivery in alternative NHS physiotherapy departments).

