### Methods of data collection

#### Patient-reported and performance-based outcomes during trial

Participants will complete outcome assessment at baseline, 3-month post-baseline and 6-month post-baseline. Baseline outcome assessment appointments will be scheduled immediately prior to participants’ initial physiotherapy session. Outcome assessments are anticipated to be conducted virtually in the participants’ own homes via phone or ‘Attend Anywhere’. However, if participants do not feel confident about completing their performance-based outcomes at home, they will be offered a choice of having their baseline assessment done in person. Outcomes to be assessed include the use of an accelerometer to measure daily PA, patient-reported outcome measures (PROMs) and performance-based outcomes. Accelerometers and PROMs will be posted to participants’ home addresses 1 week prior to outcome assessment appointments. A 150-cm tape measure will be included for standardisation of one of the performance-based tests (figure-of-8 walking test: Table 4) [47]. Participants will be asked to complete PROMs prior to assessment appointments so the session can be used to collect performance-based outcomes and answer any questions. A stamped, addressed envelope will be included for return of accelerometers (including simple fitting instructions and a belt to secure the accelerometer) and PROMs to the ROH. If accelerometers and PROMs are not returned within 2 weeks of their assessment appointment, participants will be contacted via text/telephone and asked to send them back at their earliest convenience.

**Table 4 Tab4:** Planned participant secondary outcome measures for randomised controlled trial

Outcome domain	Instrument	Administered at	Rationale
Physical activity	Short-Form (7 questions) International Physical Activity Questionnaire [48]	Baseline, 3 months, 6 months	Primary aim of physiotherapy intervention. Has demonstrated reliability and validity [48]
Adherence to PA/exercise recommendations	Section B of the Exercise Adherence Rating Scale (6 items) [49]	Baseline, 3 months, 6-month post-baseline	Primary aim of the physiotherapy intervention. Has demonstrated reliability [49] and validity [50]

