### Data analysis

#### Quantitative

The primary quantitative data analysis will be descriptive [19, 31]. A CONSORT diagram will outline the number of participants who were identified, recruited, commenced and finished treatment, and the recruitment rate (number/month and number approached/number recruited) will be reported as a percentage [29]. Where possible, reasons for refusal and dropout during the intervention will be recorded and reported. A Shapiro–Wilk test will test the normality of continuous data (e.g. PROM and accelerometer data), and the mean and 95% confidence intervals will be reported for each. The number of non-completed/partially completed PROMs, performance measures and accelerometer data at each timepoint will be expressed as a percentage. Partially completed PROM and accelerometer data will not be included in the data analysis, but potential reasons, including practicality, will be discussed in the interviews.

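### Objective 2.4 words its accelerometer measure per device and names no participant denominator for the 70% mark, so the choice of base can decide whether the mark is met

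*Protocol article*

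**What the plan says.** In the protocol article, Table 3, Objective 2.4 (marked S, a secondary feasibility outcome) asks whether an accelerometer is feasible and acceptable as the primary outcome of a later randomised trial. Three places bear on how the yield is counted:

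- The method-of-assessment cell gives the percentage "of accelerometers returned to research staff with valid data", together with interviews.
- The success-criteria cell gives "≤ 70% of accelerometer data collected at 6-month post-baseline". The validity rule follows: "Accelerometer data will be considered valid if it has been recorded for ≥ 10 h" on at least 4 of 7 days, one of them at a weekend.
- Data analysis, Quantitative, says that non-completed or partially completed PROMs, "performance measures and accelerometer data at each timepoint will be expressed as a percentage".

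None of the three names a denominator. On logistics, the section on patient-reported and performance-based outcomes says "Accelerometers and PROMs will be posted to participants’ home addresses 1 week prior to outcome assessment appointments". It foresees non-return and plans a reminder ("If accelerometers and PROMs are not returned within 2 weeks of their assessment appointment"), but it does not say how an unreturned device is counted.

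**The concern.** What the definitive trial needs to know is how many of the people recruited will yield a usable 6-month record. The measure is counted in devices. Because devices go out shortly before each appointment, someone who has already left the trial would presumably be sent none at 6 months, and so would be absent from a per-device count. The wording can also be taken as the share of returned devices that hold valid data, in which case unreturned devices drop out too.

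On either device-based reading, losses can raise the percentage compared with 70% without adding a single analysable record. The accelerometer could then pass its numerical criterion although the yield among recruited participants is below 70%. If the base is not fixed beforehand, it can also be chosen after the counts are known.

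**Working it through.** **The plan's own figure.** The 70% mark is a chosen cut-off with no calculation behind it, so there is nothing to reproduce. I treat it as a minimum. The printed sign says the opposite, but the stop level of ≤ 50% in Objective 2.2 shows that low completeness is meant to count as failure.

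**Inputs.** From the documents: a target of up to 35 recruited (Sample size), the 70% mark and the validity rule (Table 3, Objective 2.4). Assumed, because the protocol gives no rates: withdrawal before the 6-month posting w, return rate r, and valid wear among returned devices v.

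**Formulas**, with counts rounded to whole people or devices:
- issued = 35 × (1 − w); returned = issued × r; valid = returned × v
- three candidate measures: valid/returned, valid/issued, valid/35

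**Main illustration** (w = 20%, r = 90%, v = 80%):
- issued = 35 × 0.80 = 28
- returned = 28 × 0.90 = 25.2, taken as 25
- valid = 25 × 0.80 = 20
- 20/25 = 80.0%; 20/28 = 71.4%; 20/35 = 57.1%

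**Other assumed rates:**

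| w | r | v | Issued | Returned | Valid | % of returned | % of issued | % of recruited |
|---|---|---|---|---|---|---|---|---|
| 0% | 100% | 80% | 35 | 35 | 28 | 80.0 | 80.0 | 80.0 |
| 0% | 90% | 75% | 35 | 32 | 24 | 75.0 | 68.6 | 68.6 |
| 10% | 100% | 75% | 32 | 32 | 24 | 75.0 | 75.0 | 68.6 |
| 10% | 100% | 80% | 32 | 32 | 26 | 81.2 | 81.2 | 74.3 |
| 20% | 90% | 80% | 28 | 25 | 20 | 80.0 | 71.4 | 57.1 |

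With no withdrawal and full return the three measures agree. Non-return alone inflates only the returned-device figure; withdrawal inflates both device figures. In the fourth row every base clears 70%, so the choice does not always change the result.

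**Valid records needed to reach 70%, by base** (0.70 × base, rounded up):
- base 35: 24.5, so 25 (25/35 = 71.4% of recruited)
- base 32: 22.4, so 23 (23/35 = 65.7%)
- base 28: 19.6, so 20 (20/35 = 57.1%)
- base 25: 17.5, so 18 (18/35 = 51.4%)

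**The case against.** The strongest reply is that the protocol never fixes a device denominator. The cell that carries the 70% speaks of data collected, in parallel with Objective 2.2, and the Data analysis section counts non-completed accelerometer data. Both can be read as a share of all expected 6-month records, which would keep withdrawn and non-returning participants in. This stands. A reader might infer that the plan removes withdrawn participants from the denominator; the documents do not say so, and the posting schedule only makes it plausible.

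Losses are also visible elsewhere. The abstract promises a description of loss to follow-up, the CONSORT diagram reports participants recruited and finishing treatment, and Objective 2.2 is a separate primary criterion on completeness. This stands in part: a reader could recover some of the yield, but none of these figures alters the statistic compared with 70%.

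Objective 2.4 is secondary. The Table 3 legend ties progression to the primary outcomes, the row has no stop level, and it also rests on interviews. That limits the weight of the point. It does not remove it, because the section on trial outcomes and success criteria has each criterion evaluated when progression is considered, and this row concerns the planned primary outcome.

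Two stronger readings are tempting and should not be drawn:
- That the definitive trial's attrition allowance would be set too small. The Discussion says other large trials will inform the sample size calculation, and nothing derives an allowance from Objective 2.4.
- That about half of recruited participants could lack data, by taking the 70% level of Objective 2.2 as a 30% withdrawal allowance (0.70 × 0.70 = 49%). That level concerns PROM and performance data collected, so it mixes withdrawal with non-completion and is not a withdrawal rate.

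Denominators are often left to a fuller document. Here, however, the article states a unit, the device, inside its table of pre-set decision criteria, and that unit does not match the objective.

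**Conclusion.** The point holds as a denominator left unspecified in a measure worded per device. Three readings are open. Valid over returned exceeds the share of recruited participants with a usable record whenever there is withdrawal or non-return; valid over issued exceeds it whenever there is withdrawal. If expected records means all recruited, the third reading is already the right one.

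The size depends wholly on assumed rates. In the main illustration the same 20 records give 80%, 71% or 57%. With 10% withdrawal, full return and 75% valid wear, they give 75% or 69%. With no loss there is no gap. The documents support saying that the base can decide whether 70% is met; they do not support saying that the yield will be overstated. This should be settled before the criterion is applied, but for a secondary feasibility outcome it does not threaten the trial.

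**What to change.** Reword the Objective 2.4 measure in Table 3 as: number of participants with a valid 6-month accelerometer record, under the stated wear rule, divided by all participants recruited, judged against the 70% mark. Report devices issued, returned and valid as the intermediate steps, so that the point of loss (withdrawal, non-return or insufficient wear) can be seen.

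In the same row, correct the printed ≤ before 70%. As it stands a low yield counts as success, and the threshold cannot be applied on any denominator until that is put right.

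The cost is the rewording of one table row, using counts that the trial would keep routinely. The downside is that the reported percentage will be lower whenever anyone withdraws or a device is not returned.

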### Methods of data collection

#### Patient-reported and performance-based outcomes during trial

Participants will complete outcome assessment at baseline, 3-month post-baseline and 6-month post-baseline. Baseline outcome assessment appointments will be scheduled immediately prior to participants’ initial physiotherapy session. Outcome assessments are anticipated to be conducted virtually in the participants’ own homes via phone or ‘Attend Anywhere’. However, if participants do not feel confident about completing their performance-based outcomes at home, they will be offered a choice of having their baseline assessment done in person. Outcomes to be assessed include the use of an accelerometer to measure daily PA, patient-reported outcome measures (PROMs) and performance-based outcomes. Accelerometers and PROMs will be posted to participants’ home addresses 1 week prior to outcome assessment appointments. A 150-cm tape measure will be included for standardisation of one of the performance-based tests (figure-of-8 walking test: Table 4) [47]. Participants will be asked to complete PROMs prior to assessment appointments so the session can be used to collect performance-based outcomes and answer any questions. A stamped, addressed envelope will be included for return of accelerometers (including simple fitting instructions and a belt to secure the accelerometer) and PROMs to the ROH. If accelerometers and PROMs are not returned within 2 weeks of their assessment appointment, participants will be contacted via text/telephone and asked to send them back at their earliest convenience.

**Table 4 Tab4:** Planned participant secondary outcome measures for randomised controlled trial

Outcome domain	Instrument	Administered at	Rationale
Physical activity	Short-Form (7 questions) International Physical Activity Questionnaire [48]	Baseline, 3 months, 6 months	Primary aim of physiotherapy intervention. Has demonstrated reliability and validity [48]
Adherence to PA/exercise recommendations	Section B of the Exercise Adherence Rating Scale (6 items) [49]	Baseline, 3 months, 6-month post-baseline	Primary aim of the physiotherapy intervention. Has demonstrated reliability [49] and validity [50]
Pain	11-point Numerical Pain Rating Scale [51]	Baseline, 3 months, 6 months	Suggested to include as a core outcome domain in international guidelines [51]. Shown excellent reliability [52] and suggested as more reliable than a visual analogue scale in patients who are older or less literate patients and more useful for demonstrating change [53]
Function: Self-report	Short-Form Hip Disability and Osteoarthritis Outcome Score (SF-HOOS)/Short-From Knee Injury and Osteoarthritis Outcome Score (SF-KOOS) [51]	Baseline, 3 months, 6 months	Suggested to include as a core outcome domain in international guidelines [51]. Have shown good levels of reliability [54, 55]
Function: Performance based	Five times sit-stand test	Baseline, 3 months, 6-month post-baseline	Direct, observable measure of physical function. Has demonstrated excellent validity and reliability when tested in home setting [56]
	Figure-of-8 walking test	Baseline, 3 months, 6 months	Direct, observable measure of physical function. Has demonstrated validity and reliability when tested at home [47]
Bothersomeness	Bothersomeness Index: 5-point Likert scale	Baseline, 3 months, 6 months	Outlined as important outcome domain by public involvement representative
Quality of life	EuroQol 5-domain instrument (EQ-5D) [51]	Baseline, 3 months, 6 months	A domain recommended by international guidelines. Has shown good reliability and validity [57]
Self-efficacy for physical activity/exercise	Self-Efficacy for Exercise Scale 9 items [58]	Baseline, 3 months, 6 months	Outlined as an important influence on behaviour change in preliminary work. Measures several aspects of self-efficacy including perceived barriers to exercise [59]. Valid and reliable [58]
Motivation regulations to participate in physical activity/exercise	Behavioural Regulation in Exercise Questionnaire-3 24 items [60, 61]	Baseline, 3 months, 6 months	Motivation was outlined as important influence on behaviour change in preliminary work. Grounded in SDT. Important stage of intervention process model. Valid [60, 62] and reliability [63]
Psychological needs satisfaction	A modified version of the Psychological Need Satisfaction in Exercise Scale [64, 65]	Baseline, 3 months, 6 months	Grounded in SDT. Important stage of intervention process model. Valid and reliable [64, 65]
Social psychological environment/perceptions of autonomy support	Health Care Climate Questionnaire 15 items [66]	3-month post-baseline	Assesses the participants perceptions of the motivational social climate provided in physiotherapy sessions. Grounded in SDT. Important stage of intervention process model. Identified as an important influence on behaviour change in preliminary work. Reliable [66]

The accelerometer will be fitted over the right anterior superior iliac spine [45, 46, 67]. Following a standardised and widely used protocol [68], participants will be asked to wear accelerometers for 7 consecutive days [43, 69–71] with removal for sleep or when in water (e.g. swimming or shower) [45, 46, 71, 72]. The patient-reported and performance-based outcomes to be assessed, including their rationale, are detailed in Table 4.

#### Collection of qualitative data

As the main aim of the qualitative component of the trial is to gain in-depth perspectives on the feasibility and acceptability of the trial intervention and associated processes, the epistemological stance is based on phenomenology [73]. Questions will initially be asked in an open manner with clarification sought if key points are identified. Participants, physiotherapists.and research staff will be invited to introduce new topics and/or issues as the discussions progress. The respective topic guides have been developed a priori with questions determined through collaboration of the trial management team which includes clinical physiotherapists, researchers with expertise in qualitative research methods and behaviour change and PPI [74].

For individuals attending semi-structured interviews and focus groups, demographic detail will be recorded to enable description of participants, intervention physiotherapists and ROH research staff, respectively.

#### Sample size

Although a formal calculation was not completed, total sample sizes of between *n* = 24 to 50 are recommended in feasibility trials and a sample of 30 [18] to 35 [75] considered sufficient to ensure normal distribution of participants. An audit of the ROH physiotherapy waiting lists suggested that approximately 65 patients with musculoskeletal pain are referred to the ROH each week, and that approximately 5% would be eligible to participate in the trial (i.e. three per week). Based on previous trials conducted at the ROH, approximately one in three of those approached consents to participate. Therefore, based on trial resources and timelines, recruitment of a target sample of up to 35 participants over a 9-month period is estimated.

### Data analysis

#### Quantitative

The primary quantitative data analysis will be descriptive [19, 31]. A CONSORT diagram will outline the number of participants who were identified, recruited, commenced and finished treatment, and the recruitment rate (number/month and number approached/number recruited) will be reported as a percentage [29]. Where possible, reasons for refusal and dropout during the intervention will be recorded and reported. A Shapiro–Wilk test will test the normality of continuous data (e.g. PROM and accelerometer data), and the mean and 95% confidence intervals will be reported for each. The number of non-completed/partially completed PROMs, performance measures and accelerometer data at each timepoint will be expressed as a percentage. Partially completed PROM and accelerometer data will not be included in the data analysis, but potential reasons, including practicality, will be discussed in the interviews.

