**Aim 2: Trial feasibility and acceptability**		
**Objective**	**Method of assessment**	**Success criteria**
**Objective 2.1**: To measure the recruitment rates of participants (P)	• Recording number (*n*) of participants who were sent a participant information sheet, number who agreed to participate and number recruited per month	**Continue without modification** • Target of *n* = 35 participants recruited in 9 months (approx. 4/month) • Conversion rate of ≥ 30% (number sent PIS/ number who agreed to participate) **Stop** • Target of *n* = 35 participants recruited takes > 12 months (less than 3/month) • Conversion rate of ≤ 15% (number sent PIS/ number who agreed to participate)
**Objective 2.2**: To measure the completeness of data collection of performance-based and patient-reported outcome measures at baseline, 3- and 6-month post-baseline (P)	• Record number of PROMs returned to trial team and number of participants who completed performance-based outcomes during virtual outcome assessments at each timepoint	**Continue without modification** • ≤ 80% PROM and performance-based data collected at 3-month post-baseline • ≤ 70% PROM and performance-based data collected at 6-month post-baseline **Stop** • ≤ 50% PROM and performance-based data collected at 3-month post-baseline • ≤ 50% PROM and performance-based data collected at 6-month post-baseline
**Objective 2.3**: To determine the feasibility and acceptability of trial-related procedures (recruitment, outcome assessment) to participants and ROH research staff ((P)	• Participants: Semi-structured interviews • ROH research staff: Focus groups	**Continue with modification** • Thematic analysis identifies that trial participants and ROH research staff are satisfied (i.e. feasible and acceptable) with trial procedures (e.g. recruitment, outcome assessment) in semi-structured interviews and focus groups respectively **Stop** • Thematic analysis identifies that trial participants and ROH research staff are not satisfied (i.e. they do not perceive it is feasible and/or acceptable) with trial procedures (e.g. recruitment, outcome assessment) in semi-structured interviews and focus groups respectively

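### The PROM completeness criterion counts forms returned while the analysis drops any partly completed form, and partial accelerometer data are excluded without a definition

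*Protocol article*

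**What the plan says.** **PROMs.** Table 3, Objective 2.2, concerns the completeness of outcome data and is marked as a primary feasibility outcome related to progression. Its method of assessment is: "Record number of PROMs returned to trial team and number of participants who completed performance-based outcomes". The thresholds for continuing are set at 80% of data collected at 3 months and 70% at 6 months. I read both as minimums, although they are printed with ≤; that is a separate matter.

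The Quantitative part of the Data analysis section then states: "Partially completed PROM and accelerometer data will not be included in the data analysis". It does not define partially completed. It also does not say whether the unit is the item, the instrument or the whole pack. The sentence before it provides for reporting: "The number of non-completed/partially completed PROMs, performance measures and accelerometer data at each timepoint will be expressed as a percentage".

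**Accelerometer.** The data collection section says "participants will be asked to wear accelerometers for 7 consecutive days". Table 3, Objective 2.4, measures the percentage "of accelerometers returned to research staff with valid data" and sets the validity rule: "Accelerometer data will be considered valid if it has been recorded for ≥ 10 h" on "≥ 4/7 days, with at least one falling on a weekend". The exclusion sentence in the analysis section does not refer to this rule.

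**Sample.** The Sample size section gives a target of up to 35 participants.

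**The concern.** The progression criterion and the analysis appear to use different definitions of PROM data. In the Objective 2.2 row, a performance test has to be completed to count, but a PROM only has to come back. If a form with a missing answer counts there and is then excluded, the percentage that decides progression can exceed the percentage that can be analysed.

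The exclusion rule is also blunt. One blank item removes the other answers on that form, or in the whole pack if the pack is the unit, even where the scale could still be scored. With at most 35 participants and means with 95% confidence intervals to be reported, that is avoidable loss.

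For the accelerometer, the proposed primary outcome of the definitive trial, the undefined word partial leaves open whether a record of four to six days is analysed or dropped.

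**Working it through.** The article states no sample-size calculation, partial-completion rate or wear rate, so there is no planned figure to reproduce. The thresholds and the sample of 35 come from the article. All rates below are assumptions, and the denominator is taken as all 35.

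**1. Returned against complete PROMs.** The 80% threshold is 0.80 × 35 = 28 forms. The 70% threshold is 0.70 × 35 = 24.5, so 25 forms. If R forms are returned and m of them are partial, the criterion is judged on R/35, while (R − m)/35 are fully complete.

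| Time | Returned R | R/35 | Partial m | Complete R − m | (R − m)/35 |
|---|---|---|---|---|---|
| 3 months | 28 | 80.0% | 1 | 27 | 77.1% |
| 3 months | 30 | 85.7% | 3 (10%) | 27 | 77.1% |
| 3 months | 30 | 85.7% | 6 (20%) | 24 | 68.6% |
| 6 months | 25 | 71.4% | 1 | 24 | 68.6% |

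In every row the threshold is met on returned forms and missed on complete forms. It need not be so: with 30 returned and 5% partial, 28.5/35 = 81.4%, and both pass.

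**2. How easily a form becomes partial.** With an assumed independent chance q that an item is left blank, a k-item form is fully complete with probability (1 − q)^k. Table 4 gives 24 items for the longest instrument whose count is stated. The counts stated or implied at 3 months sum to 7 + 6 + 1 + 1 + 5 + 9 + 24 + 15 = 68; the other instruments' counts are not given.

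| q | k = 24 | k = 68 |
|---|---|---|
| 0.5% | 0.887 | 0.711 |
| 1% | 0.786 | 0.505 |
| 2% | 0.616 | 0.253 |

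The 68-item column applies only if the whole pack is one all-or-nothing unit.

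**3. Accelerometer under two readings.** Let each day be valid independently with assumed probability p.

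- *Partial means fewer than seven valid days.* P(kept) = p^7.
- *Partial means failing the Table 3 rule.* P(kept) = the sum, over a valid weekdays (0 to 5) and b valid weekend days (1 or 2) with a + b ≥ 4, of C(5,a)p^a(1−p)^(5−a) × C(2,b)p^b(1−p)^(2−b).

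| p | All seven days | Table 3 rule | Records of 35 |
|---|---|---|---|
| 0.80 | 0.210 | 0.937 | 7.3 against 32.8 |
| 0.90 | 0.478 | 0.988 | 16.7 against 34.6 |
| 0.95 | 0.698 | 0.997 | 24.4 against 34.9 |

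Under the first reading, the extra loss relative to the Table 3 rule runs from (0.997 − 0.698) × 35 = 10.5 to (0.937 − 0.210) × 35 = 25.4 records. Under the second reading the extra loss is zero.

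**The case against.** The strongest reply has four parts.

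- **The accelerometer rules can be read together.** The only standard for usable records is the one in Table 3, and a four-day rule has a purpose only if shorter records are usable. A reader might infer that the plan contradicts its own validity rule and would throw away most valid records. The documents do not establish that, because partial is undefined and can mean failing the rule. This part stands: the point is an ambiguity.
- **Partial completion is reported.** The analysis section expresses non-completed and partial PROMs, performance measures and accelerometer data as percentages at each timepoint, and reasons are to be explored in interviews. The shortfall will be visible, so a flat statement that completeness is overstated goes too far. But success is judged against the Table 3 criteria, and that percentage does not enter Objective 2.2. Visibility does not change the decision rule.
- **The mismatch is confined to PROMs.** Accelerometers must carry valid data and performance tests must be completed. No sentence says outright that a form with a blank item counts as collected; this follows from the method column's wording. That limits the claim to what can happen.
- **The analysis is descriptive and item-level scoring may sit in another document.** The outcome means feed no Table 3 criterion, and the Discussion says other trials will inform the future sample size. Detailed scoring rules can fairly be left elsewhere. The blanket exclusion, however, is stated here, and so is the return-based measure.

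**Conclusion.** The point holds for PROMs and is an ambiguity for the accelerometer.

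For PROMs, a primary progression criterion is measured on returned forms while the analysis excludes partial ones. The progression figure can therefore exceed the analysable data. Near the threshold a single partial form is enough (28 returned, 27 complete), and with 30 returned it takes three. Whether this happens depends on a partial-completion rate that the documents do not give.

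For the accelerometer, the extra loss runs from none to about 10 to 25 of 35 records. The upper figures need both the seven-day reading and an assumed independent daily probability of 0.95 to 0.80.

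A reader might go further and infer that little could be analysed, or that the 3- and 6-month results would look optimistic because less engaged participants drop out of the analysis. The documents support neither. They give no rates, and they say nothing on how partial responders differ from others.

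**What to change.** - **Table 3, Objective 2.2.** Count a PROM as collected only if it can be scored, with all recruited participants as the denominator. Report the number returned and the number fully complete beside it.
- **Data analysis, Quantitative, PROMs.** Define partially completed per instrument. Score such forms by the instrument's own missing-item rule where one exists, and exclude only scales that cannot be scored.
- **Data analysis, Quantitative, accelerometer.** State that every record meeting the Objective 2.4 validity rule is analysed, so that the exclusion applies only to records failing it.

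The cost is a few sentences and a little programming, with no extra data collection. The completeness percentage may come out slightly lower than a count of returns.
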